#### Health economic evaluation

We will estimate the difference in total costs for MBT-DH compared to MBT-IOP and the difference in clinically relevant effects of the treatments. By dividing the difference in costs by the difference in effectiveness, the incremental cost-effectiveness ratio (ICER) will be estimated. The ICER represents the extra amount of money that has to be invested to gain one extra unit of effect (or, conversely, the amount of money that will be saved if one unit of effect is lost).

In the economic evaluation, all relevant costs and effects will be taken into account. This means that we will use a so-called societal perspective, which is preferred in economic evaluations in the Netherlands [82]. The costs will include *all* costs, that is, intervention costs, direct and indirect medical costs, as well as productivity losses and costs accruing elsewhere in the health care system. From the societal perspective, clinically relevant effects are those effects that are meaningful for society. Moreover, in order to be able to compare effects between different interventions in health care, effects should be expressed in generic terms. We will therefore use QALYs and will express the cost-effectiveness of each intervention and the ratio between these cost-effectiveness estimates as cost per QALY. The use of QALYs is advised in guidelines for cost-effectiveness analysis, especially when main effects are expected in quality of life [82,83].

Our primary cost-effectiveness ratio will be estimated using empirical data only and therefore a 3-year time horizon will be used, which is equal to the trial duration. Cost data are generally highly skewed, and QALY scores and ICER values are not distributed normally in most cases. Therefore, the uncertainty intervals around the mean costs, mean effects and mean ICER values will be estimated using bootstrap simulations with at least 1000 replications [84-86]. These results will be graphically presented in a cost-effectiveness plane. Various societal willingness-to-pay values will be used to estimate net monetary benefits. These net monetary benefits are then used to derive cost-effectiveness acceptability curves.

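### The economic section defines the ICER correctly, then adds a ratio of per-arm cost-per-QALY figures that cannot be a cost per QALY, and plans an ICER interval that may not be interpretable

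*Protocol article*

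**What the plan says.** All of this is in the protocol article, section Health economic evaluation, unless another section is named.

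- The first paragraph gives the comparative measure: "By dividing the difference in costs by the difference in effectiveness, the incremental cost-effectiveness ratio (ICER) will be estimated".
- The second paragraph chooses QALYs as the unit of effect and says the authors will "express the cost-effectiveness of each intervention and the ratio between these cost-effectiveness estimates as cost per QALY".
- The third paragraph fixes the horizon ("a 3-year time horizon will be used, which is equal to the trial duration") and the treatment of uncertainty: "the uncertainty intervals around the mean costs, mean effects and mean ICER values will be estimated using bootstrap simulations with at least 1000 replications".
- It then adds a plot on the cost-effectiveness plane and a net-benefit analysis ("Various societal willingness-to-pay values will be used to estimate net monetary benefits"), from which acceptability curves are to be built.

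Three other sections matter. Research aims and hypotheses makes cost-effectiveness the second aim and expects MBT-IOP to be the more cost-effective arm. Background says MBT-DH may cost about twice as much as MBT-IOP. The Discussion accepts that the two programmes may turn out equally effective and differ only in cost.

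**The concern.** The section describes two different comparative quantities and gives both the label of a cost per QALY. The first, the ICER, deserves it. The second is each arm's average cost per QALY and the ratio of those two averages. That ratio is a pure number and does not say what an additional QALY costs.

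The stated hypothesis, that one arm is more cost-effective than the other, could easily be tested by comparing per-arm averages. With costs near 2:1, that comparison would favour MBT-IOP almost whatever the QALY gain, and it leaves willingness to pay out altogether.

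The second issue is the interval around the ICER. If the QALY difference may be zero, bootstrap replicates fall on both sides of zero and the ICER jumps between large positive and large negative values. At stake is the headline result for the trial's second aim.

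**Working it through.** The documents give no cost, QALY or ICER figure, so there is nothing of the plan's own to reproduce. All costs, QALYs, standard deviations and willingness-to-pay values below are assumptions. The only documented inputs are the 45 per arm (Sample size and power calculation), the 3-year horizon, the 1,000 replicates and the rough 2:1 cost relation (Background).

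**1. Units and content of the ratio.** Write C for mean cost, E for mean QALYs, D for MBT-DH and I for MBT-IOP.

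- Ratio of per-arm figures = (C_D/E_D) / (C_I/E_I). Euros per QALY divided by euros per QALY leaves no unit.
- ICER = (C_D − C_I) / (E_D − E_I), in euros per QALY.

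| C_D, E_D | C_I, E_I | Ratio of per-arm figures | ICER |
|---|---|---|---|
| 40,000, 2.0 | 20,000, 1.9 | 20,000 / 10,526 = 1.9 | 20,000 / 0.1 = 200,000 |
| 40,000, 2.5 | 20,000, 1.5 | 16,000 / 13,333 = 1.2 | 20,000 / 1.0 = 20,000 |
| 60,000, 2.0 | 30,000, 1.0 | 30,000 / 30,000 = 1.0 | 30,000 / 1.0 = 30,000 |
| 40,000, 2.0 | 30,000, 1.5 | 20,000 / 20,000 = 1.0 | 10,000 / 0.5 = 20,000 |
| 60,000, 1.5 | 30,000, 1.5 | 40,000 / 20,000 = 2.0 | undefined |

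Rows 3 and 4 share a ratio but have different ICERs, so the ratio does not determine the ICER. In rows 1 and 2 the ratio moves from 1.9 to 1.2 while the ICER falls tenfold.

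**2. How the ratio behaves at 2:1 costs.** The ratio is (C_D/C_I) / (E_D/E_I). If total costs are 2:1, it falls below 1 only when MBT-DH yields more than twice the QALYs of MBT-IOP. With a maximum utility of 1, nobody can exceed 3 QALYs in 3 years. Since 3 / 1.5 = 2, the ratio cannot favour MBT-DH once MBT-IOP averages 1.5 QALYs.

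**3. Net monetary benefit on the same examples.** Incremental net benefit = λ × (E_D − E_I) − (C_D − C_I). At λ = 80,000, row 1 gives 8,000 − 20,000 = −12,000 and row 2 gives 80,000 − 20,000 = +60,000. Both ratios exceed 1, yet the decisions differ. In row 5 the net benefit is −30,000 at any λ, so it stays defined where the ICER does not.

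**4. The bootstrap ICER.** Assume a QALY SD of 0.6. The standard error of the difference is 0.6 × √(2/45) = 0.126. Averaged over trials, the share of replicates with a negative QALY difference is about Φ(−gain / (0.126 × √2)). That is 0.29 at a gain of 0.1 and 0.003 at a gain of 0.5.

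A simulation agrees. It used 400 trials of 45 per arm with 1,000 replicates each, lognormal costs with means of 60,000 and 30,000 and an SD of 25,000:

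| True gain | True ICER | Replicates with negative QALY difference | Middle 95% of trials' mean replicate ICER | Percentile interval covers truth |
|---|---|---|---|---|
| 0.1 | 300,000 | 30% | about −1.6 million to 2.1 million | 97% |
| 0.5 | 60,000 | 0.2% | about 33,000 to 158,000 (median 62,000) | 97% |

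At a gain of 0.1, the mean of the replicate ICERs was negative in 30% of trials. Coverage does not expose the problem; interpretation does. When MBT-DH costs more, a negative ICER means it is dominated. Yet on the number line that value sorts below the small positive ICERs that favour MBT-DH most, so an interval running through both has no usable order.

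**The case against.** The strongest reply is that the disputed sentence is loose wording for the ICER. It sits in a paragraph whose purpose is to choose QALYs as the effect unit, the ICER is defined correctly one paragraph earlier, and nothing later uses a ratio of ratios. That may well be the intention. But the sentence names a figure for each intervention and then a ratio between the two, so its literal meaning is a different quantity, and an analyst following it would compute the wrong thing. The reply lowers the likely harm but leaves the sentence wrong.

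On the bootstrap, the reply is stronger. Bootstrapping an ICER is a recognised method and behaved well at a gain of 0.5. The plan already contains the plane, net monetary benefit and acceptability curves, which are the standard safeguards.

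Three stronger readings may tempt a reader, and the document supports none of them:

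- That the ICER interval is invalid as such. It fails only where the QALY difference may be zero or change sign.
- That the plan averages replicate ICERs. The wording "the uncertainty intervals around the mean costs, mean effects and mean ICER values will be estimated using bootstrap simulations" is ambiguous, and a mean ICER can also be the ratio of mean differences.
- That the cost and QALY differences will be crude. The article is silent on covariates, which may be left to a fuller plan, and unadjusted differences in a randomised trial are unbiased.

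**Conclusion.** The point holds in two parts of unequal weight.

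The ratio of per-arm figures is wrong as written. This follows from units and algebra and needs no assumption; the assumed values only show how far the ratio and the ICER can part (1.9 against EUR 200,000, and 1.2 against EUR 20,000). It should be corrected because it concerns the measure for the second stated aim.

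The ICER interval is a conditional caution. It becomes uninterpretable if replicates cross quadrants, which is plausible because the Discussion itself allows equal effectiveness. How likely that is cannot be taken from the documents. The 30% figure rests on an assumed gain of 0.1 QALY and an SD of 0.6, while the article expects MBT-DH to do better and plans for a medium difference on the BSI, with no QALY effect stated.

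**What to change.** 1. Delete the ratio of per-arm figures. State that incremental cost per QALY, the mean cost difference over the mean QALY difference, is the only comparative ratio.
2. State that the ICER point estimate is computed from the mean differences and is not an average of replicate ICERs.
3. Report no ICER interval when replicates cross quadrants; show the planned plane instead.
4. Base inference on a bootstrap interval for the incremental net monetary benefit at stated willingness-to-pay values, alongside the planned acceptability curves.

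Adjusting the QALY difference for baseline EQ-5D and the cost difference for baseline TiC-P cost is an optional gain in precision and corrects no error in the document.

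The cost is a few sentences of analysis wording. No new data are needed, and the bootstrap and net-benefit calculations are already planned.

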## Discussion

Both MBT-DH and MBT-IOP have shown promise in the treatment of patients with BPD [2,15-19]. Yet, extant studies suggest that MBT-DH may be twice as costly as MBT-IOP. This cost difference makes MBT-IOP potentially a more cost-effective treatment than MBT-DH. On this basis, there is a need for an RCT comparing the efficacy and cost-effectiveness of MBT-DH and MBT-IOP.

The present paper outlines the study protocol for such a head-to-head comparison of MBT-DH and MBT-IOP in terms of their efficacy and cost-effectiveness in the context of a multisite study in the Netherlands. The study aims to answer a number of important questions in the field. First, this will be the first trial directly comparing the efficacy of MBT-DH and MBT-IOP. Second, this promises to be the first study that entails a state-of-the-art cost-effectiveness component for both MBT-DH and MBT-IOP. Given considerable differences in treatment intensity, and thus costs of the two treatment programmes, the results of this study promise to inform decisions not only concerning treatment referral, but also with regard to maximizing the use of health care resources in a climate of decreasing health expenditure. Another important goal of the final aim of the study, which focuses on predictors of change, is to provide information that will contribute to the optimization of treatment effects and health care resources. For instance, it may well be that both treatments have equal effectiveness and differ only in terms of cost. If this were the case, health care resources should be devoted to the less costly variant (probably MBT-IOP, due to its lower intensity). However, even if it is found that both treatments differ only in terms of their costs, there may still be a subgroup of patients that may need the more intensive intervention, MBT-DH, to derive benefit. In this scenario, MBT-DH would still be indicated as a cost-effective treatment in a subgroup of patients, and it would be crucially important to identify the features of this subgroup, to enable this intervention to be offered specifically to the patients who need this more intensive treatment format. Therefore, this study also aims to identify potential predictors of response to both MBT-IOP and MBT-DH, with the aim of facilitating treatment selection.

## Abbreviations

APA: American Psychiatric Association
BDI-I: Beck depression inventory
BPD: Borderline personality disorder
BSI: Brief symptom inventory
CTQ: Childhood trauma questionnaire
ECR: Experiences in close relationships
GAF: Global assessment of functioning
GSI: Global severity index
ICER: Incremental cost-effectiveness ratio
IIP-64: Inventory of interpersonal problems
MATE: Measurements in the addictions for triage and evaluation
MBT: Mentalization-based treatment
MBT-DH: Day hospital mentalization-based treatment
MBT-I: Introductory course to mentalization-based treatment
MBT-IOP: Intensive outpatient mentalization-based treatment
PAI-BOR: Personality assessment inventory-borderline
QALY: Quality-adjusted life-year
RCT: Randomized controlled trial
RFQ: Reflective functioning questionnaire
RMET: Reading the mind in the eyes test
SCID-I: Structured clinical interview for DSM-IV axis I personality disorders
SCID-II: Structured clinical interview for DSM-IV axis II personality disorders
SIPP-118: Severity indices of personality problems
SSHI: Suicide and self-harm inventory
TAU: Treatment as usual
TiC-P: Trimbos and Institute for Medical technology assessment questionnaire on costs associated with psychiatric illness
